##### Optimal ‘cut-off’ for HCV RDT read-time

The time to positive HCV RDT under 5 min compared with RNA positivity will be assessed, including at 1 min intervals and the time turned positive.

##### Proportion ‘overtreated’ for hepatitis C

The proportion of participants ‘overtreated’/‘unnecessarily treated’ for hepatitis C in the same-day treatment model (those who are HCV antibody positive at 5 min but RNA negative), where participants were prescribed hepatitis C treatment or initiated hepatitis C treatment and later received a hepatitis C RNA negative test result will be calculated. The proportion of this group experiencing adverse events will also be described.

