Importantly, if a participant’s antibody test was positive in <5 min, it did not imply that all participants had virus present, with a positive predictive value of 62%.^23^ In particular, the accuracy of the shortened read-time of the OraQuick rapid hepatitis C antibody test to identify patients with viraemia is greatly reduced among those who had recently been treated and achieved sustained virological response (SVR).^23^ Therefore, excluding those previously treated improves the accuracy of the 5 min read-time result in detecting only patients with viraemia.

Considering these accuracy outcomes, there are two potential utilities of the proposed shortened read-time of OraQuick rapid hepatitis C antibody tests. First, by reducing the need for unnecessary reflexive RNA testing among those who return a non-reactive result by 5 min given the accuracy to exclude individuals without current infection. Second, and the focus of this study, is the potential utility of using the 5 min read-time result to identify those with current infection and initiate same-day presumptive treatment for hepatitis C. The key risk of presumptive treatment of people relates to treating people with hepatic decompensation or other significant comorbidities, prior to receipt of recommended laboratory investigations. This risk can be minimised by following clear protocols on medical history taking, including a physical examination for clinical signs and symptoms of underlying conditions that might be a contraindication. In addition, at the individual level, treating those without current infection may result in them experiencing side effects of DAAs, similar to those who are treated for their current infection.

Models of care that seek to further simplify clinical pathways may reduce consultation times and reduce unnecessary costs of testing, enabling resources in LMIC to be better targeted and reduce wastage. The potential utility of this particular model depends on the balance of reducing testing costs and improving linkage to care against overtreatment, and the relative cost and availability of commodities and the underlying HCV prevalence in specific countries (figure 1). It is important to note that the acceptability of such an approach to both patients and providers, and to policy-makers, must also be established and will influence any future utility of this approach outside of a research setting.

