#### Assessing outcome 1: impact of same-day treatment initiation model on treatment uptake and cure (arm 2 vs arm 1)

The proportion of participants initiating hepatitis C treatment and cured in the simplified care model (arm 1) compared with the same-day treatment care model (arm 2) will be calculated.

The outcome of treatment uptake will be a binary outcome measured by the proportion of participants who are RNA positive and are prescribed treatment and who self-report initiating treatment. The outcome of cure will be measured by the proportion who achieve SRV among those prescribed treatment. Analyses will be conducted using a per-protocol basis, with patients analysed according to the appropriate treatment allocation and study arm following eligibility and exclusion study criteria. Those who are enrolled in arm 2 and later treated via arm 1 study procedures are excluded from primary analyses.

All available binary outcomes will be analysed at the patient level using mixed-effects logistic regression models with random intercepts for clinic and fixed effects for interventions. Models will adjust for covariates, based on any differences in participant characteristics between arm 1 and arm 2 at baseline. These covariates may include: opioid substitution therapy status, injecting frequency, history of incarceration and housing status. ORs and 95% CIs will be reported.

Where data are available, treatment uptake and cure outcomes from arms 1 and 2 will also be compared with available historical data specific to each study country (Armenia, Georgia and Tanzania) and/or globally.

Primary research question #2: What is the feasibility of implementing a decentralised hepatitis C simplified care model (arm 1) and the same-day treatment care model (arm 2) in the varied healthcare settings in the three study countries (Armenia, Georgia and Tanzania)?

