#### Assessing outcome 3: comparative cost-effectiveness of same-day model versus simplified model (arm 2 vs arm 1)

A mathematical model will be used to estimate average hepatitis C-related costs and quality-adjusted life years per person for a theoretical cohort of 100 people in each country under three scenarios: (1) no treatment; (2) the simplified care model and (3) the same-day treatment model. Prevalence of hepatitis C antibodies and RNA in each country will be based on study data. The effect of the different models (arm 1 simplified care model and arm 2 same-day treatment model) on linkage to care and treatment uptake will be based on the pooled study outcomes across countries, and costs calculated using a decision tree structure capturing the cascade of care. The average country-specific cost per person in each scenario will be estimated from study data, using a health systems perspective (ie, consumables, medicines, health provider time and other costs identified by project staff as relevant for intervention delivery) and a societal perspective (ie, also including lost productivity among people with hepatitis C). For each country, health-related quality of life weights will be estimated using data from the EQ-5D-5L tool in each country. The incremental cost-effectiveness ratio (difference in cost divided by difference in quality-adjusted life years) will be calculated for the simplified care scenario compared with the no treatment scenario, and for the same-day treatment scenario compared with the simplified care scenario.

Estimates of average cost per person and treatment uptake for the simplified care and same-day treatment models (including the cost of the participants overtreated) in each country will be used as inputs to a national dynamic transmission model, which will be used to estimate the potential population-level benefits of scaling up each model of care.

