##### Time to initiate treatment

The time from HCV antibody RDT to prescription and dispensing of first 4 weeks of DAAs, and to self-report taking first tablet of treatment will be calculated, and compared across arms. These will be calculated both among those who were HCV antibody positive (arm 2) and also among those confirmed RNA positive (arms 1 and 2) and initiated hepatitis C treatment.

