### Participant acceptability

A participant acceptability substudy will employ qualitative methods using in-depth, semi-structured interviews with participants of arm 1 and arm 2 to examine their experiences of, perceptions and attitudes about accessing hepatitis C testing and treatment through the study, and specifically their views on starting hepatitis C treatment on the same day, prior to the RNA result being available, and ideas for improving models of care.

All participants of the hepatitis C trial will be informed that as part of the study, they may be invited to participate in qualitative interviews.

Interview participants will be purposively sampled to recruit participants that meet the following criteria:

Participants in arm 1 who test RNA positive.Participants in arm 2 who test hepatitis C antibody positive at 5 min and RNA positive.Participants in arm 2 who test antibody positive at 5 min, RNA negative and did start treatment.Participants in arm 2 who test antibody positive at 5 min, RNA negative and did not start treatment (ie, those who received the medication but never took medication).

A total of approximately 50 participants will be recruited, with 20 participants in Armenia, 16 participants in Georgia and 14 participants in Tanzania. Where possible, interviews will be conducted by community researchers.

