### Data monitoring

The trial will be monitored by an independent data safety and monitoring board with an independent statistician, clinical experts and community representatives, with at least one representative from each implementing country. There will be predefined periodic analysis if the data safety and monitoring board is concerned about any of the safety end points (serious adverse events, proportion ‘over-treated’, treatment failures).

Access to de-identified data will be limited to study investigators. The Data Safety Monitoring Board terms of reference were included in the ethics applications.

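### The adverse event proportion in overtreated arm 2 participants is taken over a group that includes people who were prescribed drug but never took it

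*Protocol article*

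**What the plan says.** The section on the proportion overtreated defines one group: arm 2 participants who are positive at 5 minutes and RNA negative, "where participants were prescribed hepatitis C treatment or initiated hepatitis C treatment and later received a hepatitis C RNA negative test result". Its next sentence is "The proportion of this group experiencing adverse events will also be described".

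Other sections bear on how that group is used:

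- **Participant acceptability** lists, as a separate interview stratum, arm 2 RNA-negative participants who "did not start treatment (ie, those who received the medication but never took medication".
- **Assessing outcome 1** counts treatment uptake among RNA-positive participants who "are prescribed treatment and who self-report initiating treatment". The same section measures cure among those prescribed treatment.
- **Time to initiate treatment** records time to prescription and dispensing, and also time "to self-report taking first tablet of treatment will be calculated, and compared across arms". In arm 2 this is done for all antibody-positive participants as well as for those confirmed RNA positive.
- **Background and rationale** names the individual harm: "treating those without current infection may result in them experiencing side effects of DAAs".
- **Assessing outcome 3** feeds overtreatment into the economic models, "including the cost of the participants overtreated".
- **Data monitoring** lists the monitoring board's "safety end points (serious adverse events, proportion ‘over-treated’, treatment failures".

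**The concern.** The word 'or' lets a prescription alone qualify. An RNA-negative person who was given a bottle and took no tablet is overtreated under this rule and sits in the denominator for adverse events. The acceptability section calls the same person someone who did not start treatment.

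Two things follow. First, the adverse event proportion is meant to describe what happens to uninfected people who receive the drug presumptively, a pathway that the adverse events section says lies outside current guidelines. Adding unexposed people to the denominator pulls that proportion down. Second, one measure carries two meanings: drug dispensed, which is a cost, and drug taken, which is the individual harm. The uptake outcome does not mix them, since it requires both a prescription and a self-reported start.

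**Working it through.** The protocol states no figure for the overtreated share or for adverse events in this group, so there is no figure of its own to reproduce. The 350 per arm has no bearing on the point.

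**Step 1. Apply the rules to records.** Take arm 2 participants who are positive at 5 minutes and were given drug.

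| Record | RNA negative | RNA positive |
|---|---|---|
| No tablet taken | Overtreated; in the adverse event denominator | Not counted as uptake |
| At least one tablet taken | Overtreated; in the adverse event denominator | Counted as uptake |

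The rule for RNA negatives does not separate the two rows. The rule for uptake does.

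**Step 2. Effect on the adverse event proportion.** Let N be the RNA-negative participants prescribed drug, f the fraction who never take it, and a the drug-related adverse event proportion among takers. Never-takers contribute no drug-related events, so

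reported proportion = a(1 − f)N / N = a(1 − f).

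The relative shortfall is f. Neither f nor a is in the protocol. With f assumed between 0% and 30% and a assumed to be 20%:

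| f | Reported proportion | Shortfall (points) |
|---|---|---|
| 0% | 20% | 0 |
| 5% | 19% | 1 |
| 10% | 18% | 2 |
| 20% | 16% | 4 |
| 30% | 14% | 6 |

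If events of any cause are counted and never-takers have them at rate b, the reported proportion is a(1 − f) + bf and the shortfall is f(a − b). The table is the case b = 0.

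**Step 3. Effect on the overtreated share.** The Background and rationale section cites a positive predictive value of 62% for a 5-minute positive. As an illustration, 38 of every 100 people prescribed drug would then be RNA negative.

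- *Never-takers removed from the numerator only:* 38(1 − f)/100 gives 36.1%, 34.2%, 30.4% and 26.6% at f = 5%, 10%, 20% and 30%.
- *Removed from numerator and denominator, same f in both RNA groups:* 38(1 − f) / [100(1 − f)] = 38% at every f.
- *Removed from both, f different by RNA status:* with 10% never-takers among RNA negatives only, 34.2 / (34.2 + 62) = 35.6%. With 10% among RNA positives only, 38 / (38 + 55.8) = 40.5%.

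The share can fall, stay the same or rise, depending on a denominator that the protocol does not name and on never-taker fractions that it does not give.

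**The case against.** **Counting prescriptions has a proper use.** Dispensed but untaken drug is a cost, and the economic analysis needs it. This stands, and it is the reason to keep a prescription-based figure beside the exposure-based one.

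**The overtreated share is overstated.** A reader might infer this from the 'or' rule. The protocol does not support it, because no denominator is named for the share and Step 3 shows that the direction depends on one. Counting every presumptive prescription is also the cautious direction for arm 2.

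**Benefit and harm are scored on opposing definitions throughout.** A reader might infer this too. The contrast with uptake is real, but the cure outcome in the same section uses those prescribed treatment as its base, so the prescribed/initiated split does not follow a benefit/harm line.

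**The wording may intend two measures, and an analysis plan is promised.** The investigators clearly distinguish dispensing from first tablet elsewhere. However, the text defines one group and one proportion and then refers back to that group for adverse events. A detail left open could wait for the analysis plan; this rule is stated.

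**The monitoring board may use another rule.** Its terms of reference are not shown. This stands: the protocol names the end point without tying it to this definition, so no error in the board's monitoring can be claimed.

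**The size is assumed.** This also stands. A purposive interview stratum shows that never-takers are foreseen, not that they are common, and participants are asked to begin treatment when drug is handed over.

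**Conclusion.** The point holds for the adverse event proportion. As written, its denominator includes people who took no drug, so the drug-related proportion among exposed uninfected participants is multiplied by (1 − f). The direction is certain for any f above 0, provided that never-takers have no events that count. The size is unknown because neither f nor the event rate is in the protocol; over the assumed range of f from 0% to 30%, an assumed 20% is reported as between 20% and 14%. The single measure also mixes drug dispensed with drug taken and differs from the rule for treatment uptake.

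Whether the overtreated share is too high cannot be settled from the protocol. The outcome is secondary and descriptive, and no primary outcome is affected. Severity is minor, and the change is a cheap improvement.

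**What to change.** Replace the single definition with two measures, each with its denominator named:

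1. **Unnecessarily prescribed or dispensed:** RNA-negative participants among all arm 2 participants prescribed or dispensed drug. Use this for cost and wastage.
2. **Overtreated by exposure:** RNA-negative participants among all arm 2 participants who self-report at least one dose. This matches the self-report element of the uptake rule.

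Compute the adverse event proportion over the RNA-negative participants in measure 2 only.

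No new data are needed. Self-reported first tablet is already planned for antibody-positive arm 2 participants, and the arm 2 procedures for visit 2 already provide a face-to-face follow-up of RNA-negative participants about their experience of treatment. The cost is one extra reported proportion and a slightly smaller adverse event denominator. No study procedure changes.

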### Process evaluation: feasibility and implementation requirements

The feasibility and implementation requirements component of this study will involve a process evaluation of the implementation of the trial to understand the contextual factors influencing the trial outcomes and the scalability of these care models trialled in arm 1 and arm 2.

This component is a mixed-methods evaluation that will involve multiple data sources, including site assessments, interviews with study staff and other stakeholders and a process monitoring and activity log that captures challenges and resolutions.

A baseline site assessment and regular site monitoring assessments will capture information about the site, how the site operates and fidelity of study implementation. Semi-structured interviews will be conducted with study site staff (doctors, nurses) and laboratory staff involved in the study to understand their perspectives on implementing this study. The structured process monitoring and activity log will be completed regularly by the study coordination team in collaboration with country teams, capturing challenges and solutions arising during study implementation.

A reflection, learning and dissemination workshop will be conducted in each country towards study close to capture perspectives of various stakeholders on the preliminary study findings and potential for scalability.

Online supplemental material 2 provides an overview of the feasibility and implementation requirements assessment, mapped to the domains of the updated CFIR.

### Participant acceptability

A participant acceptability substudy will employ qualitative methods using in-depth, semi-structured interviews with participants of arm 1 and arm 2 to examine their experiences of, perceptions and attitudes about accessing hepatitis C testing and treatment through the study, and specifically their views on starting hepatitis C treatment on the same day, prior to the RNA result being available, and ideas for improving models of care.

All participants of the hepatitis C trial will be informed that as part of the study, they may be invited to participate in qualitative interviews.

Interview participants will be purposively sampled to recruit participants that meet the following criteria:

Participants in arm 1 who test RNA positive.Participants in arm 2 who test hepatitis C antibody positive at 5 min and RNA positive.Participants in arm 2 who test antibody positive at 5 min, RNA negative and did start treatment.Participants in arm 2 who test antibody positive at 5 min, RNA negative and did not start treatment (ie, those who received the medication but never took medication).

A total of approximately 50 participants will be recruited, with 20 participants in Armenia, 16 participants in Georgia and 14 participants in Tanzania. Where possible, interviews will be conducted by community researchers.

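### The acceptability interview criteria leave out arm 2 participants who were reactive at 5 min, RNA negative and declined same-day treatment, and they do not name decliners as a group to seek

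*Protocol article*

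**What the plan says.** The section Participant acceptability describes qualitative interviews with participants of both arms, covering among other things "specifically their views on starting hepatitis C treatment on the same day, prior to the RNA result being available". On selection it states: "Interview participants will be purposively sampled to recruit participants that meet the following criteria". Four groups follow:

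1. "Participants in arm 1 who test RNA positive".
2. "Participants in arm 2 who test hepatitis C antibody positive at 5 min and RNA positive".
3. "Participants in arm 2 who test antibody positive at 5 min, RNA negative and did start treatment".
4. Arm 2, reactive at 5 min and RNA negative, who "did not start treatment (ie, those who received the medication but never took medication".

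On numbers it says: "A total of approximately 50 participants will be recruited, with 20 participants in Armenia, 16 participants in Georgia and 14 participants in Tanzania". Interviews are allocated by country only; no group has a number of its own.

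Three other places matter. Arm 2 study procedures, Visit 1, makes same-day treatment an offer based on the 5 min result and requires the RNA sample to be drawn before any medication is handed over. Aims and research questions lists participant acceptability as a secondary question. Background and rationale says that acceptability to patients has to be shown and will affect whether the approach is used outside research.

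**The concern.** An offer can be declined. Someone who declines to start treatment before the RNA result is well placed to say why presumptive treatment is not acceptable. The fourth group looks designed to reach non-starters, but its parenthesis limits it to people who accepted the bottle and then did not use it. Someone who declined the bottle at the visit has made a different and more explicit choice.

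What is at stake is the range of views heard. Among RNA-negative arm 2 participants, the interviews could cover those who took the tablets and those who took the bottle away, but not those who said no. For RNA-negative people treatment would have been unnecessary, so their reasons for declining bear on the overtreatment question that the trial also examines.

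**Working it through.** No sample-size formula applies; this is a question of who fits the stated criteria.

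**The plan's own figure.** 20 + 16 + 14 = 50 interviews, which agrees with the stated total of about 50.

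**Can decliners exist and be classified?** Yes. Treatment is offered (Arm 2 study procedures, Visit 1). A positive 5 min result leads to a blood sample for RNA, taken before any medication is given. A person who gives the sample and declines the bottle therefore has a known RNA result. The acceptability section also says that all trial participants are told they may be invited to interview, so nothing in the article prevents an approach to them.

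**Arm 2 participants reactive at 5 min and offered same-day treatment, set against the four criteria:**

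| RNA result | Response to the offer | Criterion met |
|---|---|---|
| Positive | Accepted | Group 2 |
| Positive | Declined | Group 2, not distinguished from acceptors |
| Negative | Started | Group 3 |
| Negative | Took the bottle, never used it | Group 4 |
| Negative | Declined, received nothing | None |

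The empty last row comes from the parenthesis in group 4. Without it, not starting treatment would have covered both kinds of RNA-negative non-starter. Group 1 cannot fill the gap, because arm 1 participants were not offered treatment before their RNA result.

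**Could another component supply these reasons?** The uptake outcome (Assessing outcome 1) and the care cascade (Assessing outcome 2) count who starts; they do not record why someone declined. The process evaluation interviews staff and other stakeholders and keeps an activity log. These may report refusals second-hand, but they are not participants' own accounts.

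**How many people are affected?** The article does not allow a figure. The sample size section presumes 85% uptake in arm 1 and a detectable difference of 7 points, so a scenario of 85% + 7 points = 92% in arm 2. With 350 starts that gives 350 / 0.92 − 350 = 380.4 − 350, or about 30 non-starters. This is not the number wanted, for three reasons:

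- Assessing outcome 1 defines uptake among RNA-positive participants. All 30 would be RNA positive and so eligible under group 2.
- 92% is a detectable-effect scenario; the same section acknowledges considerable uncertainty about uptake.
- Non-starting is not the same as declining. The article attributes the 15% shortfall in arm 1 to loss to follow-up, and in arm 2 some people will be ineligible for same-day treatment on clinical grounds.

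**The case against.** The strongest reply is that the choice of groups for some 50 qualitative interviews is a design preference, that a journal article condenses the full qualitative protocol, and that the sample is far from acceptors only. Much of this stands:

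- Group 2 sets no condition on accepting or starting, and purposive sampling lets the team choose an RNA-positive decliner deliberately.
- Group 4 already captures one form of non-acceptance.
- No group has a reserved number, so the lack of one for decliners does not set them apart.
- Group 1 neither accepted nor refused presumptive treatment.

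A reader might infer more: that everyone who refuses is shut out, that the substudy will therefore overstate acceptability, or that a share of the 30 non-starters can be counted as excluded. The documents do not support these readings. RNA-positive decliners are in the frame. The interviews estimate no proportion that could be biased upward. The 30 are RNA positive by definition, so no RNA-negative share can be taken from them.

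The appeal to condensation does not remove the remaining gap. The article states the fourth criterion and defines it; this is an explicit rule, not detail left to another document.

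**Conclusion.** The point holds in a narrow form. As written, the criteria exclude arm 2 participants who were reactive at 5 min, RNA negative and declined the offer. RNA-positive decliners may be interviewed, but nothing directs the team to seek them. Their reasons fall squarely within the substudy's stated purpose and are not collected from participants elsewhere in the plan as shown.

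The number of people concerned is unknown and could be very small. The conclusion rests on the wording of the four criteria and on same-day treatment being an offer, not on any assumed refusal rate. It affects a secondary qualitative outcome and leaves the primary outcomes, the sample size and the quantitative analysis untouched. It is a minor but worthwhile correction.

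**What to change.** Widen the fourth criterion so that it covers RNA-negative arm 2 participants who were offered same-day treatment and declined it, as well as those who received the medication and did not use it. In addition, name decliners, whatever their RNA result, as a group to be purposively sought within the existing total of about 50 interviews, as available.

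A fixed quota is not advisable while the size of the group is unknown. For example, 2 to 3 per country over three countries would take 6 to 9 of the 50 interviews (12% to 18%), and 3 would be 21% of the 14 in Tanzania. Sought as available, the change costs a few interviews in the other groups, an edit to the sampling list and whatever ethics notification that edit requires. No clinical procedure changes.
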